## Abstract

**Background:**

Estimates suggest that approximately 1 in 10 patients admitted to hospital experience an adverse event resulting in harm. Methods to improve patient safety have concentrated on developing safer systems of care and promoting changes in professional behaviour. There is a growing international interest in the development of interventions that promote the role of patients preventing error, but limited evidence of effectiveness of such interventions. The present study aims to undertake a randomised controlled trial of patient-led teaching of junior doctors about patient safety.

**Methods/Design:**

A randomised cluster controlled trial will be conducted. The intervention will be incorporated into the mandatory training of junior doctors training programme on patient safety. The study will be conducted in the Yorkshire and Humber region in the North of England. Patients who have experienced a safety incident in the NHS will be recruited. Patients will be identified through National Patient Safety Champions and local Trust contacts. Patients will receive training and be supported to talk to small groups of trainees about their experiences. The primary aim of the patient-led teaching module is to increase the awareness of patient safety issues amongst doctors, allow reflection on their own attitudes towards safety and promote an optimal culture among the doctors to improve safety in practice. A mixture of qualitative and quantitative methods will be used to evaluate the impact of the intervention, using the Attitudes to Patient Safety Questionnaire (APSQ) as our primary quantitative outcome, as well as focus groups and semi-structured interviews.

**Discussion:**

The research team face a number of challenges in developing the intervention, including integrating a new method of teaching into an existing curriculum, facilitating effective patient involvement and identifying suitable outcome measures.

**Trial Registration:**

Current controlled Trials: ISRCTN94241579

## Background

Patient safety is an international health priority [1]. Estimates suggest that approximately 1 in 10 patients admitted to National Health Services hospitals in the UK is involved in an incident which results in harm to patients [2] with a subsequent cost to the NHS of over £2 billion [3]. Strategies to reduce patient safety incidents have shifted the focus from a person centred approach where errors are viewed as occurring as the result of the individual, to developing a systems approach whereby individual error is accepted and mechanisms are put in place to ensure that error is reduced in the environment in which it occurs [3,4].

There is an increasing international drive to involve patients in safety initiatives [5]. However recent reviews of the literature have highlighted: a lack of initiatives to promote patient and/or carer involvement in patient safety; major gaps in our knowledge about the nature and impact of patient involvement; little evidence of the feasibility or effectiveness of patient centred interventions and uncertainty over their acceptability amongst patients and health professionals [5,6]. One role for patients in improving patient safety is in teaching health professionals as part of educational interventions. Patient-led teaching for healthcare professionals has been reported to be effective in terms of learner satisfaction and improved performance in key areas such as communication skills [7]. Patient narratives involving patients sharing their stories with professionals are now widely employed as part of medical training and clinical skills acquisition [7,8]. Patient safety is a particularly appropriate topic for such teaching as patients can bring real lived experiences of error and harm to the classroom, describe the personal impact of such errors and facilitate discussion around the error. There is a paucity of research which examines the use of patient stories in a safety context; although preliminary research suggests that this is a feasible method for communicating concerns about patient safety to healthcare professionals [6]. The present study aims to develop an intervention based on patients as teachers in training junior doctors about patient safety and to evaluate the impact of this intervention on safety attitudes in a randomised controlled trial.

## Method

### Design

The study is a randomised controlled trial conducted in the North of England with a two step approach covering West and North/East Yorkshire.

### Setting

The study will be conducted in two postgraduate medical schools in the Yorkshire and Humber region, West Yorkshire (WY) and North East Yorkshire and North Lincolnshire (NEYNL). In West Yorkshire, teaching on patient safety takes place at two sites; in the trial one site will receive the intervention (Harrogate Hospital) and a second site will receive the control (Airedale Hospital). In NEYNL, teaching takes place at five sites (Scunthorpe, Scarborough, Hull, Grimsby and York Hospitals). There are ten teaching sessions in total with each of the hospitals being responsible for delivering some of the patient safety teaching. There is variation in the number of sessions provided at each site, e.g. Grimsby, n = 1; York, n = 3. Teaching at these sites commences in January 2011 for approximately 8 weeks. The first phase of the study in the West Yorkshire Foundation School will allow for the refinement of our methodology and serve as a trial for our outcome measures. In NEYNL Foundation School, the intervention and control arm will run in parallel sessions, trainees and participants will be randomly assigned to either group on the day of teaching.

### Context

The intervention will be incorporated into the mandatory training of the first year postgraduate training for patient safety, i.e. Foundation Year 1 (FY1) trainees.

### Sample

Two separate populations will be recruited a) patients and b) trainee doctors

#### a) Patients

Two types of patients will be recruited and will receive training to deliver the intervention. Firstly patient safety champions will be identified through a national network (National Patient Safety Agency (NPSA) and Action against Medical Accidents (AVMA)). This network of trained volunteers provides advocates of patient safety and a source of stories about the personal impact of error in diagnosis, treatment and care. Secondly, local patients will be identified from patient and public involvement contacts and existing patient safety research networks. There are 16 teaching sessions that require patient input. We therefore anticipate recruiting 4-5 local patient safety champions and 4-5 national patient champions to deliver this teaching in both regions. This will mean that each patient is not overburdened with the number of sessions they deliver or the time and travel required participating in the study.

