#### b) Trainee doctors

In West Yorkshire there are currently 290 FY1 trainees enrolled. Eleven teaching sessions are conducted with approximately 26 trainees attending each session (intervention or control). In NEYNL, approximately 150 trainees will be enrolled as FY1. Ten teaching sessions on patient safety are conducted; therefore approximately 15 trainees attend each session (Figure 1). Each session will be equally divided, with approximately 7-8 trainees receiving the control and 7-8 receiving the intervention, as illustrated with Scarborough in Figure 1.

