### Sample Size calculation

In NEYNL, there are 150 trainees that will be allocated into 20 groups of 7-8 trainees. Assuming an intracluster correlation coefficient of 0.05 this gives a design effect of 1.3. The effective sample size, therefore, is 150/1.3, which is 115. This gives us approximately 80% power to demonstrate an effect size of 0.53.

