### Procedure

Trainees in the control group will be informed that their course is being evaluated and they will be asked to complete questionnaires during their training. Trainees in the intervention group will receive the same information, and in addition, they will be informed that their teaching will consist of patients delivering stories about their experience of a safety incident. Using the patient experience is an established part of medical teaching and it is not anticipated that trainees will refuse to be taught in this manner. Those who do not wish to take part in either the control or intervention group will not be asked to complete questionnaires.

Participants in West Yorkshire will consent to the study at the beginning of the teaching session. At the intervention site (Harrogate) teaching will be delivered in the morning session (approximately three hours of teaching). Two patient champions will speak about their experiences which will be based around the three themes covered in the control group, namely, prescribing, teamwork and effective communication. The control group (Airedale) will receive three sessions also on these topics, communicated using the standard methods of teaching, which includes PowerPoint presentations and small group work. In the afternoon, at both sites, all trainees will receive training on: Personal organisation, Handover, Prioritisation and Transfusion. Questionnaires will be completed before the intervention and returned on the day of teaching; participants will also be required to complete the questionnaires at the end of the teaching session and one month later.

Trainees in NEYNL will be consented on the day of the study. Any trainees objecting to taking part in the intervention will be assigned to the control group, which will run in parallel to the intervention. The control will receive the standard teaching and the intervention will receive the intervention. These sessions will run simultaneously.

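### The 8-10 patient teachers recur across sessions, so intervention groups sharing a speaker are correlated; neither the design effect of 1.3 nor group-level Huber-White errors allow for this

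*Protocol article*

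**What the plan says.** On the supply of teachers, the protocol's section on patients states "There are 16 teaching sessions that require patient input" and continues "We therefore anticipate recruiting 4-5 local patient safety champions and 4-5 national patient champions to deliver this teaching in both regions". That makes 8-10 patients for both regions.

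On speakers per session, the Procedure section says for West Yorkshire "Two patient champions will speak about their experiences". No number is given for NEYNL. The section on development of the intervention places a third patient at every session as observer and reserve, which implies two speakers there too. The same section leaves the content of each talk largely to the patient who gives it.

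On clustering, the Sample Size calculation says "In NEYNL, there are 150 trainees that will be allocated into 20 groups of 7-8 trainees", then "Assuming an intracluster correlation coefficient of 0.05 this gives a design effect of 1.3", "The effective sample size, therefore, is 150/1.3, which is 115" and "This gives us approximately 80% power to demonstrate an effect size of 0.53". The section on trainee doctors adds that in NEYNL "Each session will be equally divided, with approximately 7-8 trainees receiving the control and 7-8 receiving the intervention", so both arms run side by side within each session.

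The Analysis section promises a regression with baseline adjustment and a Huber-White correction for clustering. It does not name the cluster. Neither section mentions teachers who are common to several groups.

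**The concern.** In this trial the speaker and the story are the intervention. If speakers differ in how far they move attitudes, two intervention groups taught by the same patient share that difference and are positively correlated. The control arm has no such component.

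The design effect counts similarity only within a group of 7-8. A robust variance clustered on the group likewise treats the ten NEYNL intervention groups as independent. Both leave out the covariance between groups with a common speaker, so the variance of the intervention mean is understated. At stake are the error rate of the main comparison, the stated power, and whether a result driven by a few compelling speakers can be told apart from an effect of patient-led teaching as a method.

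**Working it through.** **Inputs.** From the Sample Size calculation: 150 trainees, 20 groups (10 per arm, about 75 trainees per arm), ICC 0.05, design effect 1.3, effect size 0.53. From the section on patients: 16 sessions, 8-10 patients. From Setting: 10 NEYNL sessions. Assumed: two-sided 5% test, two speakers per NEYNL session, all 8-10 patients serving NEYNL, reuse as balanced as possible, unit total variance.

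**Speaking slots.** All sessions: 16 x 2 = 32 slots; 32/10 = 3.2 to 32/8 = 4 per patient. NEYNL: 10 x 2 = 20 slots; 20/10 = 2 to 20/8 = 2.5 per patient. If fewer patients serve NEYNL, reuse is heavier.

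**The plan's own figure.** Design effect = 1 + (m - 1) x 0.05, which is 1.30 at m = 7 and 1.325 at m = 7.5. Effective N = 150/1.3 = 115. Normal-theory power at 0.53 with 57.5 per arm is 81.1%; a t-test on 113 df gives 80.4%; a design effect of 1.325 gives 80.5%. The stated 80% is reproduced.

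**Variance with shared speakers.** Let speakers carry the whole ICC in the intervention arm, each of the two contributing 0.05/2 = 0.025. If speaker i takes k_i of the 10 sessions:

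- Control mean: 0.05/10 + 0.95/75 = 0.01767.
- Intervention mean: 0.025 x (sum of k_i squared)/100 + 0.95/75.

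| NEYNL roster | Sum of k squared | Speaker term | Variance of difference | SE | Power at 0.53 |
|---|---|---|---|---|---|
| No reuse (20 patients, once each) | 20 | 0.0050 | 0.03533 | 0.188 | 80% |
| 10 patients, twice each | 10 x 4 = 40 | 0.0100 | 0.04033 | 0.201 | 75% |
| 8 patients (four x 3, four x 2) | 36 + 16 = 52 | 0.0130 | 0.04333 | 0.208 | 72% |

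Power is the normal probability below 0.53/SE - 1.96. With 10 patients the effective N is 4/0.04033 = 99 and the detectable effect is 0.56. The 10-patient row equals the case of five fixed pairs, each teaching two sessions: the intervention design effect is then 1 + 14 x 0.05 = 1.70. None of these figures includes the gain from baseline adjustment.

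**Type I error.** Simulation under no mean difference (20,000 runs per scenario), Huber-White errors clustered on the 20 groups, t on 19 df, ICC 0.05, remainder of the ICC independent between groups:

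| Speakers' share of ICC | 8 patients | 10 patients |
|---|---|---|
| 25% | 6.6% | 6.0% |
| 50% | 6.9% | 6.5% |
| 75% | 7.7% | 6.8% |
| 100% | 8.6% | 7.2% |

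With no sharing the same test gives 5.6%, because there are only 20 clusters. Fixed pairs carrying the whole ICC give 8.7% (8 patients) and 7.8% (10). An ICC of 0.10 arising wholly from speakers gives 8.7-11.0%.

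**When the rest is a session effect.** Each NEYNL session holds both arms, so an effect common to its two halves cancels in the contrast, while group-level clustering still counts it. With control groups given a group effect equal in variance to the speakers', and the rest of the ICC a shared session effect (8,000 runs), a 50% speaker share gives 5.6% (8 patients) and 4.9% (10). A 25% share gives 4.2% and 3.6%. A separate run of this case spans 3.4-5.8%.

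**The case against.** The strongest case on the other side has four parts.

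1. **Size and direction.** A reader might infer that the type I error is about 9% and that the trial's test is therefore liberal. The protocol does not support that. It gives no speaker variance. Values near 9% at ICC 0.05 need eight patients who account for the whole ICC, and part of the excess over 5% comes from having 20 clusters. A session effect common to the parallel arms pulls the other way and can take the rate below 5%. The net direction is undetermined. This part stands, and the size can only be given as a conditional range.

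2. **Cluster unit.** Clustering on the teaching group is an inference, and a condensed article may leave the unit to an analysis plan. That the unit is not named is not the fault raised here. But the Sample Size calculation knows no cluster other than the group of 7-8. With freely rostered pairs, sessions overlap through different patients, so no one-way speaker cluster exists for the Huber-White method to use. A later choice of cluster unit would not by itself solve this, and who spoke must be recorded at the time.

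3. **Target of inference.** If conclusions were limited to these particular patients, speaker variation would not enter the error in this form. The Abstract, however, presents a trial of patient-led teaching as a method.

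4. **Rostering.** Requiring fixed speaker pairs would be too strong. Eight patients give four pairs for ten sessions, the reserve arrangement can break a pair, and burden and travel limit the roster. This stands; fixed pairs are at most an option.

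**Conclusion.** The structural point holds. On the protocol's own numbers speakers must recur in NEYNL, groups with a common speaker are correlated if speakers differ, and neither the design effect of 1.3 nor group-level robust errors account for it.

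The consequence is moderate and conditional. At ICC 0.05 the type I error is about 6-9% over a speaker share of 25-100%, against 5.6% without sharing. It is about 3-6% at a share of 25-50% when the remainder is a session effect shared by the arms. Power at 0.53 falls to about 72-75% if speakers carry the whole ICC, and the stated 80% holds only if shared speakers add no variance.

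This rests on two speakers per NEYNL session, all 8-10 patients serving there with balanced reuse, patients regarded as a sample of possible teachers, and the group as the cluster. The documents do not show that the planned test is anti-conservative on balance. They show that its standard error does not match the design.

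**What to change.** - **Conduct.** Record which patients actually spoke at each NEYNL session, including any reserve who stepped in, and spread speakers over sessions as evenly as the roster allows. Fixed pairs are optional.
- **Analysis.** Include the session as a stratum, since both arms run in each one, and fit a speaker random effect in the intervention arm with small-sample degrees of freedom. Do not rely on group-level Huber-White errors alone.
- **Sample size text.** State that the 80% is conditional on no shared-speaker variance, and give the 72-80% range with its assumptions.

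The cost is a line on the attendance record, a sentence in the analysis and a sentence in the power statement. The downside is somewhat wider intervals and fewer degrees of freedom. With 8-10 speakers over ten intervention groups the speaker variance will also be imprecisely estimated, which should be acknowledged when the result is reported.

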#### b) Trainee doctors

In West Yorkshire there are currently 290 FY1 trainees enrolled. Eleven teaching sessions are conducted with approximately 26 trainees attending each session (intervention or control). In NEYNL, approximately 150 trainees will be enrolled as FY1. Ten teaching sessions on patient safety are conducted; therefore approximately 15 trainees attend each session (Figure 1). Each session will be equally divided, with approximately 7-8 trainees receiving the control and 7-8 receiving the intervention, as illustrated with Scarborough in Figure 1.

**Figure 1 F1:**
[figure not shown]
**Approximate number of participants assigned to each site**.

### Sample Size calculation

In NEYNL, there are 150 trainees that will be allocated into 20 groups of 7-8 trainees. Assuming an intracluster correlation coefficient of 0.05 this gives a design effect of 1.3. The effective sample size, therefore, is 150/1.3, which is 115. This gives us approximately 80% power to demonstrate an effect size of 0.53.

### Ethical Approval

Ethical approval for the study was granted by the National Research Ethics Committee in February 2010.

### Procedure

Trainees in the control group will be informed that their course is being evaluated and they will be asked to complete questionnaires during their training. Trainees in the intervention group will receive the same information, and in addition, they will be informed that their teaching will consist of patients delivering stories about their experience of a safety incident. Using the patient experience is an established part of medical teaching and it is not anticipated that trainees will refuse to be taught in this manner. Those who do not wish to take part in either the control or intervention group will not be asked to complete questionnaires.

Participants in West Yorkshire will consent to the study at the beginning of the teaching session. At the intervention site (Harrogate) teaching will be delivered in the morning session (approximately three hours of teaching). Two patient champions will speak about their experiences which will be based around the three themes covered in the control group, namely, prescribing, teamwork and effective communication. The control group (Airedale) will receive three sessions also on these topics, communicated using the standard methods of teaching, which includes PowerPoint presentations and small group work. In the afternoon, at both sites, all trainees will receive training on: Personal organisation, Handover, Prioritisation and Transfusion. Questionnaires will be completed before the intervention and returned on the day of teaching; participants will also be required to complete the questionnaires at the end of the teaching session and one month later.

Trainees in NEYNL will be consented on the day of the study. Any trainees objecting to taking part in the intervention will be assigned to the control group, which will run in parallel to the intervention. The control will receive the standard teaching and the intervention will receive the intervention. These sessions will run simultaneously.

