### Analysis

We will undertake a regression based analysis adjusting for any clustering effects using the Huber-White approach as implemented in STATA. We will adjust for baseline test scores.

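### Trainee information differs by arm, and nothing places consent or the baseline APSQ before the arm is known

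*Protocol article*

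**What the plan says.** All of this is in the protocol article.

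- **Information, control arm (Procedure section):** "Trainees in the control group will be informed that their course is being evaluated and they will be asked to complete questionnaires during their training".
- **Information, intervention arm (Procedure):** the same, "in addition, they will be informed that their teaching will consist of patients delivering stories about their experience of a safety incident".
- **Refusal (Procedure):** the text goes straight on to say that "it is not anticipated that trainees will refuse to be taught in this manner", and then that "Those who do not wish to take part in either the control or intervention group will not be asked to complete questionnaires".
- **West Yorkshire:** Setting assigns the intervention to Harrogate and the control to Airedale. Procedure says "Participants in West Yorkshire will consent to the study at the beginning of the teaching session".
- **NEYNL:** Setting says that "trainees and participants will be randomly assigned to either group on the day of teaching". Procedure says "Trainees in NEYNL will be consented on the day of the study", and sends anyone who objects to the intervention to the control group.
- **Baseline timing:** the West Yorkshire paragraph of Procedure requires the first questionnaires before the intervention. Measures requires the APSQ and the knowledge test before the training session. Neither relates the baseline to the moment when the arm becomes known.
- **Analysis:** "We will adjust for baseline test scores".

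**The concern.** Adjusting for baseline is safe because a covariate measured before allocation cannot be affected by it. Here the information given to trainees depends on arm, and information specific to an arm can ordinarily be given only once the arm is known. Two things are then at risk.

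First, the decision to take part may depend on the arm. Those who decline fill in no questionnaires, so analysing the remainder as randomised would not recover them.

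Second, the baseline APSQ may already carry an effect of allocation. It is a self-reported attitude scale and the primary quantitative outcome, and Measures reports feedback that patient stories stir emotion in learners. A trainee who has just been told that harmed patients are about to speak may answer differently from one told only of a course evaluation. Adjusting for such a score could remove part of a real effect or add a spurious one.

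**Working it through.** **The plan's own figure.** Sample Size calculation gives 150 trainees in 20 groups of 7-8 and an intracluster correlation of 0.05.

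- Design effect = 1 + (m - 1) x 0.05. With m = 7 this is 1.30, and 150/1.30 = 115.4. With m = 7.5 it is 1.325, and 150/1.325 = 113.2.
- Power for 0.53 SD with 57.5 effective trainees per arm is 0.811 by the normal approximation and 0.804 by the noncentral t. With the design effect of 1.325 it is 0.805 (normal approximation). Two-sided 5% is assumed, because the article does not state the level.

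The stated 115, 80% and 0.53 reproduce. The present point does not alter them; 0.53 SD serves only as a yardstick below.

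**Order of events, West Yorkshire.** The arm is set by site and consent is taken when the session starts. Allocation therefore precedes consent. This follows directly from the text.

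**Order of events, NEYNL.**

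1. Allocation and consent both fall on the day of teaching; their order is not given.
2. Procedure describes the information by arm, with the patient stories disclosed only to the intervention group. Taken literally, the arm is known when the information is given.
3. The possibility of refusal is raised immediately after that disclosure, and only those willing to take part are asked for questionnaires. The sequence this suggests is information, decision, questionnaires.
4. The objector rule requires that trainees know of the intervention when they object. It does not settle whether they have been allocated by then.
5. The only limit on the baseline is that it comes before the session.

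So, in NEYNL, knowledge of the arm before the decision to take part is implied by steps 2 and 3. A baseline after disclosure is probable but not stated.

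**What a shifted baseline would do.** In a regression with baseline adjustment,

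adjusted effect = (difference in follow-up means) - slope x (difference in baseline means).

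If disclosure moves the intervention arm's baseline by s SD and leaves its follow-up score unchanged, the bias is -(slope x s). The article gives neither quantity. With assumed slopes of 0.5 to 0.7 and assumed shifts of 0.1 to 0.3 SD in absolute size:

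| Slope | Shift (SD) | Absolute bias (SD) | As share of 0.53 |
|---|---|---|---|
| 0.5 | 0.1 | 0.05 | 9% |
| 0.5 | 0.3 | 0.15 | 28% |
| 0.7 | 0.1 | 0.07 | 13% |
| 0.7 | 0.3 | 0.21 | 40% |

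An upward shift lowers the estimated effect, a downward shift raises it, and no shift gives no bias.

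**The case against.** The best reply is that the NEYNL sequence is nowhere set out. The objector rule can be read as follows: everyone hears about the intervention, objectors speak up at consent, and the draw comes afterwards. The requirement that questionnaires be completed before the intervention and handed in on the day also fits forms filled in earlier, and that sentence stands in the West Yorkshire paragraph. West Yorkshire, where the order is certain, is described as a phase for refining methods and trying out the measures. A short article may also leave the running order of the day to the full protocol.

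Much of this stands. A reader might infer that the article says the NEYNL baseline is taken after disclosure; it does not. What the reply does not remove is the stated rule that information differs by arm. That is a positive instruction rather than an omission, and it fits poorly with consent before allocation.

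Two further inferences are tempting and unsupported. One is that the bias would usually run towards no effect: nothing in the document indicates which way disclosure would move APSQ answers, or whether it would move them at all. A 0.3 SD shift from a single sentence of information would be 57% of the effect the teaching is sized to show (0.3/0.53), so the upper end of the illustration should not be taken as likely. The other is that refusals will differ between arms: the article expects none, the training is mandatory, and no refusal rate is given. Moving objectors to control is a separate problem and is not relied on here to show bias.

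**Conclusion.** The point holds as a weakness in the stated procedure. Information is arm-specific, and no section puts consent or baseline ahead of knowledge of the arm. In West Yorkshire consent follows allocation. In NEYNL, the powered phase, knowledge of the arm before the decision to take part is implied, and before the baseline APSQ is probable; neither is stated outright.

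Participation may therefore depend on arm, and the adjusting covariate may already reflect it. The document does not determine the size or the sign. The 0.05 to 0.21 SD illustration rests wholly on the assumed slope and shift, and on the shift touching baseline alone. The point should be corrected because the remedy is cheap and because no later analysis choice can restore a clean baseline or the data of those who declined.

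**What to change.** For NEYNL, set the order of the day in the Procedure section:

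1. Give all trainees in a session the same information, describing both teaching formats (standard teaching and patient stories).
2. Take consent, and hear any objections, from the whole group of about 15.
3. Collect the completed baseline APSQ and knowledge questionnaires from that whole group.
4. Only then draw and announce the allocation and divide the room.

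The shared information should name the patient stories rather than refer vaguely to two formats. Otherwise trainees could object only after hearing their allocation, and arm-related withdrawal would return. In West Yorkshire the arm is set by site, so no re-ordering on the day can place consent before allocation.

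The cost is a few minutes of re-ordering and one common information sheet. Control trainees would learn of the other format, which the parallel sessions would largely reveal anyway.

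### NEYNL trainees who object to the intervention are assigned to control, so for them preference replaces randomisation and the arms may not be comparable

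*Protocol article*

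**What the plan says.** Setting, in the protocol article, describes parallel intervention and control sessions in NEYNL, where "trainees and participants will be randomly assigned to either group on the day of teaching". The section on trainee doctors adds an even split: "Each session will be equally divided, with approximately 7-8 trainees receiving the control and 7-8 receiving the intervention".

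Procedure gives the consent steps. "Trainees in NEYNL will be consented on the day of the study", followed by the rule at issue: "Any trainees objecting to taking part in the intervention will be assigned to the control group".

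Three other statements in Procedure bear on the point:

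- Intervention trainees receive the same information as controls and, in addition, "they will be informed that their teaching will consist of patients delivering stories about their experience of a safety incident".
- On refusals, "it is not anticipated that trainees will refuse to be taught in this manner".
- On data collection, "Those who do not wish to take part in either the control or intervention group will not be asked to complete questionnaires".

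Measures has the attitude and knowledge questionnaires given to every trainee in both groups. Analysis specifies regression with Huber-White adjustment for clustering and adjustment for baseline scores. The article does not say whether objection comes before or after the random draw, or in which group objectors are analysed.

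**The concern.** Random allocation makes the two arms alike apart from the teaching. The objector rule sets this aside for a self-selected subgroup and moves its members one way only: all of them end up in control and none in the intervention arm. The primary quantitative outcome is an attitude score (APSQ), and reluctance to be taught about safety by patients could well be related to that score.

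The main comparison is affected. NEYNL is the only phase in which the article describes random assignment of trainees (in West Yorkshire the arm is fixed by site), and it is the only phase in the sample size calculation. This is a stated allocation rule, not a detail left for an analysis plan. If objection precedes the draw, objectors have no randomised arm, and no later analysis can supply one.

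The information procedure adds a difficulty. If only intervention trainees hear about the patient stories, only they have reason to object, and like-minded trainees in control are never identified. Dropping the known objectors at analysis would then also be one-sided.

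**Working it through.** **Inputs from the article.** Sample Size calculation: "there are 150 trainees that will be allocated into 20 groups of 7-8 trainees"; intracluster correlation 0.05; design effect 1.3; effective sample size 115; about 80% power for an effect of 0.53 SD. The arms are equal, so 75 each. No significance level is given; two-sided 5% is assumed.

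**The article's own figure.** Design effect = 1 + (7 − 1) × 0.05 = 1.30, and 150/1.3 = 115, or 57.5 per arm. Then 0.53 × √(57.5/2) = 2.84, and 2.84 − 1.96 = 0.88, which gives power of 81.1% (80.4% with a t-test on 113 df). The stated 80% reproduces. The objector rule does not enter this calculation.

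**Inputs that must be assumed.** Let f be the share of trainees who would object, and D the gap in mean outcome (non-objectors minus objectors, in SD). The article gives neither, so ranges are shown. The true effect is set to zero and objectors are analysed as controls.

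**Formulae.**

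- If objectors are moved after the draw, the intervention arm has 75(1 − f) trainees and control has 75(1 + f). The same numbers arise if objectors go to control first and the rest are then split equally.
- Objector share in control = 150f / [75(1 + f)] = 2f/(1 + f); share in intervention = 0.
- Bias = D × 2f/(1 + f). A positive D favours the intervention and a negative D favours control.
- SE = √1.3 × √(1/[75(1 − f)] + 1/[75(1 + f)]), used in a normal test for the type I error.

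**Worked case, f = 10%, D = 0.5.** Share = 15/82.5 = 18.2%. Bias = 0.182 × 0.5 = 0.091 SD. SE = √1.3 × √(1/67.5 + 1/82.5) = 0.187. Bias/SE = 0.486, which gives a two-sided type I error of 7.7%.

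| f | D (SD) | Objectors in control | Bias (SD) | Type I error |
|---|---|---|---|---|
| 0% | any | 0% | 0 | 5.0% |
| 2% | 0.5 | 3.9% | 0.020 | 5.1% |
| 5% | 0.5 | 9.5% | 0.048 | 5.8% |
| 5% | 1.0 | 9.5% | 0.095 | 8.0% |
| 10% | 0.5 | 18.2% | 0.091 | 7.7% |
| 10% | 1.0 | 18.2% | 0.182 | 16.3% |

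If sessions are instead kept at exactly 75 and 75 with all objectors in control, the share is 2f and the bias is slightly larger: 0.10 SD rather than 0.091 SD in the worked case.

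**Effect of baseline adjustment.** The table is before adjustment. Assume a baseline-to-follow-up correlation of 0.5 and the same gap at both times. The residual gap is then D × (1 − 0.5), so 0.091 SD becomes about 0.045 SD. The SE falls by √(1 − 0.25) to about 0.162, and the type I error is about 6%.

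**If objectors are analysed in the arm drawn.** There is no selection bias, but the effect is diluted to 0.53 × (1 − f): 0.519, 0.503 and 0.477 SD at 2%, 5% and 10%, with power 79.5%, 77.0% and 72.5%.

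**The case against.** The strongest reply is that the rule may never be used. Procedure does not expect refusals, because patient experience is an established part of medical teaching. With no objectors there is no bias; at 2% and a 0.5 SD gap it is negligible. This stands as a limit on size. It does not rescue the rule, which is unsuitable for any objector who does appear.

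A second reply is that the teaching is mandatory, so an objector must be taught somewhere, and assignment to control may only describe where. The analysis set could be defined in a fuller document. This is possible. But the wording makes objectors members of the control group, and Measures gives the questionnaires to everyone in both groups, so the natural reading is that they contribute control data.

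Three stronger readings are tempting and are not supported:

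- **That the bias favours the intervention.** This needs objectors to hold poorer safety attitudes, which the article nowhere says. It notes that patient stories provoke emotion and that trainees may have experienced incidents as patients or carers. Such trainees might object for personal reasons and score higher, which would reverse the sign.
- **That the whole NEYNL randomisation is broken.** If objection comes before the draw, trainees without objection are still validly randomised. The fault is then confined to counting objectors as controls.
- **That Procedure contradicts itself.** The no-questionnaire sentence can be read as covering people who decline the whole study, whereas the objector rule covers those who decline the intervention only. It is unclear whether the sentence reaches the second group, but no contradiction is established.

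**Conclusion.** The point holds in a limited form. The Procedure rule does not fit the random assignment stated in Setting, and it makes arm depend on preference in one direction. If objectors are counted as controls, comparability is lost and the estimate can be biased either way.

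The size depends on an objection rate and an outcome gap that the article does not give. With a 0.5 SD gap and no baseline adjustment, the range is from about 0.02 SD (2% objecting) to about 0.09 SD (10%), against a target effect of 0.53 SD. The planned adjustment would remove part of it, about half under the assumptions shown. A serious distortion would need objection to be much more common than the article expects. Correction is still warranted, because the flaw lies in how trainees are allocated and is easily put right before the teaching starts.

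**What to change.** Reconcile Setting and Procedure along these lines:

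1. On the teaching day, obtain consent and ask every NEYNL trainee about willingness to attend either session before any allocation.
2. Randomise only those willing to attend either.
3. Let objectors attend the control session for their mandatory teaching, but keep them outside the randomised comparison and report their number.
4. Analyse anyone who changes their mind after allocation in the arm drawn.
5. Remove the sentence that assigns objectors to the control group, and say whether the no-questionnaire sentence covers trainees who object to the intervention only.

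**Cost.** The analysed sample shrinks by the number of objectors. With 75(1 − f)/1.3 effective trainees per arm and the design effect held at 1.3, power for 0.53 SD is 80.5%, 79.2% and 77.1% at 2%, 5% and 10% objecting. The consent procedure also changes: all trainees, including those later drawn to control, learn of the patient-led session before allocation, whereas at present only intervention trainees are to be told. Analysing objectors in the arm drawn is a valid alternative only if the draw comes first, and it costs more power at the same objection rate.
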